### Renal angina index calculation

To ascertain fulfillment or absence of renal angina on the day of admission, the renal angina index will be calculated as previously described (Additional file 2) [5]. An RAI of ≥8 will be interpreted as fulfillment of renal angina.

### MediData Rave™

Data entry of the variables of interest will be performed by the investigators and clinical research coordinators at the participating sites using a web-based data base: MediData Rave™. Rave™ is a commercial system designed to capture, manage, and report clinical research data. Through this system, each participating site is assigned a unique code, as identified by the study team. If responses to the initial inclusion and exclusion criteria provided by the individual performing the data entry fulfill study criteria, the system will dynamically generate the remainder of the patient casebook, opening the “gateway” for the site to enter additional data for an enrolled patient. When eligibility is determined, the system will guide the data entry personnel at each site to enter the clinical variables of interest. All participating sites will use the same case report forms (CRFs). The electronic CRFs will be designed and monitored by the representatives in the Data Management Center (DMC) at Cincinnati Children’s Hospital Medical Center (CCHMC) based on the paper CRFs developed by the clinical team. The DMC team from the coordinating site, the Center for Acute Care Nephrology (CACN) at CCHMC, will be the only individuals that can access and extract the data for all other sites. Other sites will have access only to their enrolled subjects in Rave™. Data management and statistical analysis will be executed at CCHMC.

### Interventions

AWARE is a non-intervention observational study. Urine collection will occur only for patients that have an indwelling urinary catheter or are scheduled for clean intermittent catheterization.

### Consent

AWARE is proposed as human subjects research with a waiver of informed consent/parental permission and assent. This waiver is pursued by the following rationale:The research involves no more than minimal risk to the subjects.The waiver does not adversely affect the rights and welfare of the subjects.The research cannot practically be carried out without the waiver or alteration. Enrolling the maximum number of PICU admissions during the study period yields the greatest and most informative amount of data. Requiring informed consent from every eligible patient causes a significant reduction in enrollment and potentially introduces selection bias into the dataset (i.e., omission of all patients from centers with limited clinical research personnel). Robust quality improvement and process improvement work in patients with acute kidney injury requires that all subjects with acute kidney injury be included in the process. Requiring informed consent leads to incomplete participation, and therefore the data gathered under an informed consent requirement reduces the reliability of the data.The research on urine collection and biomarker measurements is reliably and confidentially performed with waiver of consent as long as the following caveats are appliedOnly urine intended for discard or waste will be used.Urine will be collected only from patients with an indwelling urinary drainage system and collection apparatus or scheduled for intermittent catheterization. Patients will not be bagged or catheterized separately/independently for the purposes of this study.

The sites participating in AWARE have obtained appropriate ethical board approval from their respective review consensus boards (Additional files 3 and 4). No site participating in the study is awaiting approval from an ethical board. Although some institutions have waived the need for consent, some require written, informed consent and this will be obtained as indicated to fulfill an additional inclusion criterion.

### Co-enrollment

Patients enrolled in AWARE may also be enrolled in other studies without exception. As AWARE is non-interventional, there is no overlap in the observation with other CACN or PICU/CICU origin studies.

### Primary and secondary outcomes

Our primary outcome is to report the epidemiology and associated outcomes of pediatric AKI worldwide (in over 30 PICUs, 12 different countries, 5 continents). This outcome is dependent on broad enrollment from participating centers. AKI is defined as KDIGO stage 2 or 3 AKI by creatinine and/or urine output criteria on Day 3 or later of PICU/CICU admission (Day 3 AKI).

Our secondary outcomes are to validate and refine the renal angina risk stratification model for prediction of Day 3 AKI.Determine if fulfillment of renal angina on Day 0 is predictive of severe AKI on Day 3 of PICU/CICU admission across the heterogeneous patient landscape of our participating centers. The AWARE data repository will be used to validate the precision of the RAI in ruling out AKI.Determine if prediction of Day 3 AKI by an RAI ≥ 8 is augmented by inclusion of urinary biomarkers alone or in combination.

Longer term outcomes to be followed include duration of mechanical ventilation, use of continuous renal replacement therapy, use of extracorporeal assist devices such as extracorporeal membrane oxygenation (ECMO) or ventricular assist devices (VADs), ICU length of stay, and mortality (Day 30 follow up).

### Sample size

The AWARE study will be the largest prospective *pediatric* AKI study describing global epidemiology, risk factors, and associated outcomes. To date, the largest prospective cohort study of AKI to date was conducted by the Beginning and Ending Supportive Therapy for the Kidney (BEST Kidney) investigators [34]. In the BEST Kidney study 18% of 29,269 patients prospectively studied after admission to 54 adult ICUs across 23 countries over 15 months developed AKI. For the AWARE study, we based our sample size estimation on the number needed to validate RAI internationally. We validated RAI in 370 PICU admissions from two different sites (average of 185 per site) in North America [5]. To be able to make RAI a universal index, we need to validate the RAI in all participating sites. Accordingly we are estimating the average number of enrolled children to be an average of 150 from each participating site with a total of approximately 5,250 children from all sites (assuming the final number of participating centers is around 35). Among the participating sites, we estimate one third to participate in urine collection, resulting in an expected approximately 1750 patients with urine biomarkers able to be measured. We are allocating each site 3 consecutive months to complete patient enrollment. Data capture can occur after the three months are complete, but no new patients are to be enrolled.

### Analysis

Analysis of data will be performed independently based on each specific aim.Data for the primary objective of describing the epidemiology of AKI will be presented as a descriptive model. The prevalence on day 0 and incidence of AKI in up to 7 days of ICU admission using KDIGO classification will be calculated for each site cohort to identify the geographical “hot spots” of pediatric AKI. The data then will be pooled into a single cohort to study the outcome of AKI. The whole cohort will be stratified on Day 3 into four sub-populations with: no AKI, AKI-KDIGO Stage 1, AKI-KDIGO Stage 2, and AKI-KDIGO Stage 3. An adjusted and unadjusted survival analysis models using log rank test and cox regression models will be used to compare the mortality rates and the need of renal replacement therapy between the 4 groups.The prognostic value of the renal angina index will be calculated on Day 0 for the development of Day 3 AKI. RAI will be evaluated as a diagnostic test and sensitivity, specificity, positive predictive value, negative predictive value, likelihood ratios, and receiver operating characteristics (ROCs) will be derived.Individual prognostic values of each of the four urinary biomarkers al one for Day 3 AKI will be calculated. The biomarkers will be tested in combination for changes in prognostic parameters and comparisons of discrimination using net reclassification improvement (NRI) and integrated discrimination improvement (IDI) will be derived. Finally, the contribution of each biomarker to the predictive model of renal angina for Day 3 AKI will be analyzed by integrating the biomarkers alone and in combination with the RAI.

Additionally, the association of renal angina index, urinary biomarker levels with clinical outcomes, including mortality, PICU length of stay, hospital length of stay, and renal replacement therapy provision, will be assessed using Chi-square test (or Fisher’s exact test for small counts) or Pearson correlation coefficient (or non-parametric Spearman correlation coefficient) based on the nature of data. Classification and regression tree analysis will be used to determine optimal decision rules for biomarker incorporation with RAI when discriminating for Day 3 AKI. In all analyses, a p-value of <0.05 will be considered statistically significant.

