The design of this prospective study has limitations. We make several assumptions with regards to the expected incidence of AKI per PICU/CICU center. Differing geographic areas included in our enrollment study list and different patient demographics may have greater or less incidence of AKI risk. Many pediatric patients have no ‘baseline’ creatinine measured prior to the time of acute illness. Our assumption of a normal creatinine clearance is based on the use of this paradigm in previous study [4]. Additionally, we assume that 33% or greater of our enrollment sites will be able to capture urine for the biomarker analysis. Perhaps the greatest limitation is that this study is being independent of financial reimbursement. Study coordinators, research coordinators, and data management specialists at each site are not compensated for the exclusive purpose of this study, which has the potential to bias the enrollment strength of each center (depending on staff enthusiasm and availability). All of these limitations can also be interpreted as strengths of the study, however. Our initial results indicate that the AWARE study will assemble a broad and heterogeneous patient repository and that the pro bono work done by our coordinating sites is robust. It is our expectation that the AWARE study will serve as a model, a proof of concept that resources are in place to facilitate broad based pediatric AKI studies, for future large scale multicenter studies that are funded and sponsored by governmental and private financial support.

AKI is a significant disease syndrome affecting a large proportion of pediatric ICU patients. Existing data indicates that patients are not just dying with AKI, but *from* AKI [35]. AWARE is a first of its kind and vital study of critically ill children that will inform the pediatric critical care nephrology community of the prevalence and associations of AKI across the globe, offering new perspectives for prediction and detection of disease.

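### The pooled analyses name no allowance for site, and about 150 children per site support neither the search for AKI hot spots nor site-level RAI validation with useful precision

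*Protocol article*

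**What the plan says.** - **Site rates.** In the Analysis section, AKI prevalence on day 0 and incidence over up to 7 days "will be calculated for each site cohort to identify the geographical" hot spots of pediatric AKI.
- **Pooling.** The next step is: "The data then will be pooled into a single cohort to study the outcome of AKI". Mortality and need for renal replacement therapy are compared across four Day 3 AKI groups by log-rank tests and Cox models, adjusted and unadjusted, with covariates not named. RAI accuracy measures and chi-square, Fisher, Pearson or Spearman analyses are also planned. A threshold of p < 0.05 applies throughout. No site term, stratification, clustered variance or shrinkage is mentioned.
- **Sample size.** The rationale is that "we need to validate the RAI in all participating sites". This leads to an "average of 150 from each participating site with a total of approximately 5,250 children from all sites". That total rests on a stated premise about how many units take part: "assuming the final number of participating centers is around 35". No target precision, event count or intraclass correlation (ICC) is given.
- **Differences between sites.** Under Sample size: "We are allocating each site 3 consecutive months to complete patient enrollment". Under Consent, some institutions waive consent, while "some require written, informed consent and this will be obtained as indicated to fulfill an additional inclusion criterion"; the same section says that requiring consent potentially introduces selection bias. The Discussion says AKI risk may differ by geographic area and patient demographics, and that coordinators are not paid for the study, "which has the potential to bias the enrollment strength of each center".

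**The concern.** The plan works at two levels, and each has a weakness.

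**Pooled level.** Unstratified log-rank, chi-square and correlation tests in their standard form treat children as independent. The protocol itself expects AKI risk to vary by area. For a pooled proportion, such as overall incidence or RAI sensitivity, an interval that disregards site is too narrow whenever the ICC is positive. For contrasts that vary within site, such as AKI stage against mortality, the main danger is confounding: units that differ in both AKI frequency and mortality can distort the association.

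**Site level.** Identifying hot spots goes beyond tabulating rates. With about 150 children from one 3-month window, a site's rate reflects chance, season, consent model, completeness of enrolment and case mix as well as geography. The number of 150 per site is also tied to validating the RAI in every site, but the Analysis section contains no such analysis, and a site of that size would measure accuracy poorly.

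At stake are the credibility of any geographical claim, the claim that the RAI holds across sites, and the stated precision of the headline incidence.

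**Working it through.** **1. The plan's own figure.** 35 sites × 150 = 5,250, and one third of that is 1,750 for the urine subset. Both reproduce. They are products, not results of a power or precision formula. The Setting section gives 32 sites and the Abstract 31; at 150 each these give 4,800 and 4,650.

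**2. Assumed inputs.** The documents give no expected AKI rate for this cohort, no expected RAI sensitivity and no ICC. They cite 18% from an adult ICU cohort and 8% to 89% from pediatric reports. I use true rates of 8–40%, sensitivity near 80%, and ICCs of 0.01–0.05.

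**3. Spread between sites by chance alone.** I simulated 32 and 35 sites of 150 children, all with the same true rate (100,000 runs each). The table shows the mean lowest and highest observed site rates, and the median ratio of highest to lowest.

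| Common true rate | Lowest to highest | Ratio |
|---|---|---|
| 8% | 4% to 13% | 3.3–3.4 |
| 12% | 7% to 18% | 2.6 |
| 18% | 12% to 25% | 2.1 |
| 30% | 22% to 38% | 1.7 |
| 40% | 32% to 48% | 1.5 |

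With no true differences, the extreme sites would still differ 1.5- to 3.4-fold.

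**4. Precision of RAI sensitivity in one site.** Cases per site = 150 × rate. Exact (Clopper–Pearson) 95% intervals:

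- 10%: 15 cases, 12/15 = 80%, CI 52–96%
- 18%: 27 cases, 22/27 = 81%, CI 62–94%
- 30%: 45 cases, 36/45 = 80%, CI 65–90%

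The Inclusion criteria restrict analysis to ICU stays of at least 48 hours. If the 150 counts all enrolled children, the numbers analysed per site are smaller still.

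**5. Pooled incidence.** At 12% with n = 5,250, the half-width under independence is 1.96 × √(0.12 × 0.88 / 5,250) = 0.88 points. The design effect is 1 + (150 − 1) × ICC, and the half-width grows by its square root.

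| ICC | Design effect | Half-width (points) |
|---|---|---|
| 0.01 | 2.49 | 1.39 |
| 0.02 | 3.98 | 1.75 |
| 0.05 | 8.45 | 2.56 |

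At 18% the half-width goes from 1.04 to 1.64, 2.07 and 3.02 points.

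**6. Where step 5 does not carry over.** AKI stage and RAI status vary among children within a site. For comparisons of outcome between such groups, the full design effect does not apply, so step 5 must not be used to inflate the standard errors of the Cox or log-rank comparisons.

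**The case against.** **Silence is not neglect.** A reader might infer that the plan ignores clustering and adjusts for nothing. The text does not support that. Adjusted Cox models are planned with covariates unnamed, so site or case mix could be among them, and clustered variances are commonly left to an analysis plan, which is not shown. Pooling into one cohort contrasts with tabulation by site; it is not a statement that children are independent. This objection stands, and the point is limited to saying that no allowance is named.

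**Not every interval is too narrow.** This also stands. No ICC or interval method is given, and the design effect applies to pooled proportions only.

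**Hot spots may be mere description.** The primary objective is called descriptive, with no ranking, test or threshold, and the Discussion already concedes that incidence may vary with geography and demographics. So it goes too far to say that the plan reads chance as geography; that is a risk. But identification of hot spots is the stated purpose of the site rates, and description with that purpose needs protection against chance and against differences between sites.

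**Validation may mean across all sites together.** The aim of validating the RAI internationally, across heterogeneous centres, allows this reading. The sample size rationale nevertheless speaks of all participating sites and sets a number per site. On either reading, no assessment of how accuracy varies between sites is named.

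**Higher AKI rates soften the figures.** True: at 40% the chance spread falls to 1.5-fold, and 45 cases narrow the sensitivity interval to 65–90%. Both remain wide for judging a single site.

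**Conclusion.** The concern holds within limits, and the plan should be changed.

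- The site rates meant to identify hot spots have no stated safeguard against chance, season, consent model, enrolment strength or case mix. Chance alone gives a 1.5- to 3.4-fold spread for assumed common rates from 40% down to 8%.
- The per-site number rests on a validation that the Analysis section does not contain. A site of 150 would give a sensitivity near 80% with a CI of 52–96% to 65–90%, assuming 15 to 45 cases.
- The pooled analyses name no allowance for site. For an assumed pooled incidence of 12%, an ICC of 0.01–0.05 takes the half-width from 0.9 to 1.4–2.6 points. For within-site contrasts the issue is mainly confounding by site.

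The total of 5,250 is arithmetically correct.

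**What to change.** 1. **Outcome models.** Stratify the log-rank and Cox analyses by site, or add a site frailty term to the Cox models.
2. **Pooled proportions.** Use cluster-robust or mixed-model intervals for pooled incidence and RAI accuracy.
3. **RAI validation.** Restate the sample size rationale as validation across sites. Summarise site-level accuracy with a random-effects model and a prediction interval.
4. **Site rates.** Report shrunken site incidences with intervals, adjusted for case mix and, where the design allows, for calendar month and consent model. Each site has one 3-month window and probably one consent model, so these two factors can be separated from site only in part. Call the result between-site variation, not hot spots.

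The cost is wider intervals, modest extra analysis and a reworded sample size rationale. No new data are required. With more than 3,500 children already enrolled at the time of writing and enrolment windows fixed, the analysis is where this can still be put right.

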**Methods/Design:**

This is a prospective observational study. We anticipate collecting data on over 5000 critically ill children admitted to 31 pediatric intensive care units (PICUs) across the world during the calendar year of 2014. Data will be collected for seven days on all children older than 90 days and younger than 25 years without baseline stage 5 chronic kidney disease, chronic renal replacement therapy, and outside of 90 days of a kidney transplant or from surgical correction of congenital heart disease. Data to be collected includes demographic information, admission diagnoses and co-morbidities, and details on fluid and vasoactive resuscitation used. The renal angina index will be calculated integrating risk factors and early changes in serum creatinine and fluid overload. On days 2–7, all hemodynamic and pertinent laboratory values will be captured focusing on AKI pertinent values. Daily calculated values will include % fluid overload, fluid corrected creatinine, and KDIGO AKI stage. Urine will be captured twice daily for biomarker analysis on Days 0–3 of admission. Biomarkers to be measured include neutrophil gelatinase lipocalin (NGAL), kidney injury molecule-1 (KIM-1), liver-type fatty acid binding protein (l-FABP), and interleukin-18 (IL-18). The primary outcome to be quantified is incidence rate of severe AKI on Day 3 (Day 3 – AKI). Prediction of Day 3 – AKI by the RAI and after incorporation of biomarkers with RAI will be analyzed.

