Despite increasing awareness of the prevalence and significance of AKI, effective therapies for this condition are lacking. This, at least in part, stems from a failure to recognize AKI before a significant degree of renal damage has already occurred. The inability to diagnose AKI expeditiously follows from the fact that the currently accepted definitions of AKI rely on changes in serum creatinine (SCr) and urine output [4]. The well-recognized limitations of SCr have been previously described [16,17]. Intensive basic and translational research has targeted the discovery of biomarkers able to uncover AKI prior to elevations in serum creatinine. To date, a number of promising candidate urinary AKI biomarkers have emerged following preliminary proteomic analyses in murine models of renal ischemia [18]. Clinical studies indicate that urinary neutrophil gelatinase-associated lipocalin (NGAL), kidney injury molecule-1 (KIM-1), interleukin 18 (IL-18) and liver-type fatty acid binding protein (L-FABP) all predict AKI in children following cardiopulmonary bypass prior to changes in serum creatinine [19-21]. Widespread clinical extrapolation of these results is challenging, however, given their derivation and validation in homogenous populations free from common co-morbidities and exposed to a uniform insult on a known time scale. New adult-specific data indicate that plasma NGAL demonstrates reasonable predictive performance in heterogeneous patients, with variable comorbidities, presenting to the emergency room [22]. Neither plasma NGAL, nor the other biomarkers listed above, have demonstrated robust efficacy in children with heterogeneous illness when tested in isolation. Additionally, select early papers utilized definitions of AKI that may have contributed to the high sensitivities subsequently achieved by urinary biomarkers [23]. Such issues may underlie these urinary biomarkers' inability to predict AKI severity, identify children who would require renal replacement therapy (RRT), and predict AKI-associated death [23-27]. In response to a need of clinical predictors of AKI, we proposed the renal angina clinical model [28,29]. In this model, a composite of clinical risk factors and clinical evidence (the renal angina index (RAI)) of acute kidney injury directs biomarker testing, akin to directed assessment of troponin I only in select patients with chest pain. This model seeks a high negative predictive value (NPV) for AKI of *not fulfilling renal angina*. Further, unlike difficult to use, severity of illness scoring systems which merely score existing injury, fulfillment of renal angina aids *prediction* of severe AKI. In relatively small, retrospective studies, we have demonstrated that the RAI offers moderate discrimination for severe AKI, prediction which improves after the incorporation of biomarkers [30]. This ‘targeting’ of biomarker testing demonstrates a methodology to optimize the utility of novel diagnostics.

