### Inclusion criteria

The inclusion criteria are designed to capture as many potential study patients as possible and are inclusive of most patients admitted to the PICU and cardiac intensive care unit (CICU). All inclusion criteria must be met and only patients with an ICU length of stay of at least 48 hours are included in data analysis (other patient data is kept for demographic data repository, but excluded from data analysis for renal angina or AKI associated outcome).In-patient in a PICU or CICUAge ≥ 90 daysAge < 25 years

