### Exclusion criteria

Maintenance hemodyialysis or peritoneal dialysis.Chronic kidney disease with a baseline estimated glomerular filtration rate (eGFR) of < 15 ml/min/1.73 m^2^.Kidney transplant within 90 days of PICU/CICU admission.Post-operative from surgical correction of cyanotic congenital heart disease within 90 days of PICU/CICU admission.Uncorrected congenital heart disease (does NOT include patients with an isolated atrial or ventricular septal defect, patent ductus arteriosus, or patent foramen ovale).Immediately following elective cardiac catheterization.

For exclusion criteria 4–6, patients admitted and then taken to the operating theater for surgical corrections requiring cardiopulmonary bypass are included for study.

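### RAI accuracy for Day 3 AKI does not separate children already at KDIGO stage 2–3 on Day 0, so persisting injury can count as successful prediction

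*Protocol article*

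**What the plan says.** All references are to the protocol article.

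- **Index test.** The section headed Renal angina index calculation states: "To ascertain fulfillment or absence of renal angina on the day of admission, the renal angina index will be calculated as previously described", with a score of 8 or more counted as positive. The Abstract describes its content: "The renal angina index will be calculated integrating risk factors and early changes in serum creatinine and fluid overload".
- **Outcome.** Primary and secondary outcomes: "AKI is defined as KDIGO stage 2 or 3 AKI by creatinine and/or urine output criteria on Day 3 or later of PICU/CICU admission".
- **Planned analysis.** Analysis: "The prognostic value of the renal angina index will be calculated on Day 0 for the development of Day 3 AKI". Sensitivity, specificity, predictive values, likelihood ratios and ROC curves follow. The four urinary biomarkers are then assessed for the same outcome, alone, in combination and added to the RAI.
- **Who is analysed.** Inclusion criteria: "only patients with an ICU length of stay of at least 48 hours are included in data analysis". The renal exclusions are maintenance dialysis, a recent kidney transplant and "Chronic kidney disease with a baseline estimated glomerular filtration rate (eGFR) of < 15 ml/min/1.73 m^2". AKI present at admission is not excluded.
- **Day 0 AKI.** The descriptive aim in the Analysis section reports Day 0 prevalence separately from incidence over up to seven days. The RAI and biomarker aims make no such split.
- **Claim for the RAI.** The Background presents it as an aid to prediction, in contrast to "severity of illness scoring systems which merely score existing injury".
- **Urine.** Abstract: "Urine will be captured twice daily for biomarker analysis on Days 0–3 of admission". The Analysis section does not say which sample enters the models.

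**The concern.** The analysis speaks of AKI developing, but the outcome is a state on or after Day 3. A child at stage 2 or 3 on Day 0 who is still there on Day 3 is a case. If the Day 0 RAI is positive, which is plausible since it contains creatinine change, that child is a true positive. The accuracy figures then mix two questions: does the RAI recognise injury already present that will persist, and does it identify children who will newly progress?

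The Background's claim concerns the second question. Without a split, a reader cannot tell how much of the reported accuracy belongs to it. RAI validation is a secondary outcome, but the Sample size section names it as the basis for the number enrolled.

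**Working it through.** **Plan's own figures.** 150 per site × 35 sites = 5,250 children, and 5,250 / 3 = 1,750 with urine. Both reproduce. Neither is built on a target sensitivity, NPV or AUC, so they do not settle this point.

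**Text check.** Test on Day 0; outcome on Day 3 or later; no requirement that the outcome be new; no exclusion of AKI at admission; only a 48-hour stay rule. No step removes or separates Day 0 stage 2–3 AKI from the accuracy analysis.

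**Illustration.** The article gives no Day 0 rate, so every input except the 5,250 is assumed:

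- 12% have Day 3 severe AKI: 0.12 × 5,250 = 630 cases and 4,620 non-cases (treating all 5,250 as meeting the 48-hour rule)
- in children at risk on Day 0: sensitivity 0.60, specificity 0.80, AUC 0.70
- children with Day 0 severe AKI: 95% RAI-positive; AUC 0.95 for those who persist
- 30% of Day 0 severe AKI resolves by Day 3
- *f* = share of Day 3 cases already severe on Day 0, from 10% to 50%

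Formulas:

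- Sensitivity, all comers = *f* × 0.95 + (1 − *f*) × 0.60
- AUC, all comers = *f* × 0.95 + (1 − *f*) × 0.70 (same non-cases, so resolvers are ignored)
- Resolvers R = 630*f* / 0.7 × 0.3
- Specificity, all comers = [(4,620 − R) × 0.80 + R × 0.05] / 4,620

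| *f* | New cases | Sensitivity, all (at risk 0.60) | AUC, all (at risk 0.70) | Specificity, all (at risk 0.80) | NPV, all / at risk |
|---|---|---|---|---|---|
| 10% | 567 | 0.635 | 0.725 | 0.796 | 0.941 / 0.942 |
| 20% | 504 | 0.670 | 0.750 | 0.791 | 0.946 / 0.948 |
| 30% | 441 | 0.705 | 0.775 | 0.787 | 0.951 / 0.954 |
| 50% | 315 | 0.775 | 0.825 | 0.778 | 0.962 / 0.966 |

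*NPV at f = 50%.* R = 315 / 0.7 × 0.3 = 135. At risk: true negatives (4,620 − 135) × 0.80 = 3,588; false negatives 315 × 0.40 = 126; NPV = 3,588 / 3,714 = 0.966. All comers add 135 × 0.05 = 6.75 true negatives and 315 × 0.05 = 15.75 false negatives: 3,594.75 / 3,736.5 = 0.962.

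*Why NPV does not rise.* The all-comer NPV is a weighted average of the NPVs in the two strata. In the Day 0 AKI stratum it is 6.75 / 22.5 = 0.30. The average could exceed the at-risk NPV only if nearly all RAI-negative children with Day 0 severe AKI recovered.

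*Resolvers and AUC.* In the worst case, resolvers outscore every case. AUC is then multiplied by 1 − R/4,620: at *f* = 50%, 0.825 × (1 − 135/4,620) = 0.80; at *f* = 10% (R = 27), 0.725 × (1 − 27/4,620) = 0.72. Both remain above 0.70 under these inputs.

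*Heavier resolution.* If 10% of children (525) have Day 0 severe AKI and half (262.5) resolve, all-comer specificity is (4,357.5 × 0.80 + 262.5 × 0.05) / 4,620 = 0.757 against 0.80.

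*Lower at-risk sensitivity.* With 0.55 instead of 0.60, *f* = 25% gives 0.2375 + 0.4125 = 0.65, and *f* = 60% gives 0.57 + 0.22 = 0.79: a rise of 10 to 24 points.

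**The case against.** **All comers may be the intended population.** Severe AKI on or after Day 3, new or persistent, is the declared endpoint, and the Discussion counts inclusion of all ICU patients as a strength. The primary outcome, descriptive epidemiology, already separates Day 0 prevalence from incidence. This stands: the all-comer estimate is a legitimate quantity, and replacing it as the main analysis would be an arguable choice of estimand. What does not follow is that it can alone support a claim to predict new injury.

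**Stronger readings that the article does not support:**

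- *That NPV, the RAI's stated target, is inflated.* Under the inputs above it is slightly lower in all comers. With 0.55 for at-risk sensitivity, *f* = 50% and no resolution, it is 3,696 / (3,696 + 157.5) = 0.959 against 3,696 / (3,696 + 141.75) = 0.963.
- *That every accuracy measure is flattered.* Day 0 AKI that resolves adds false positives and lowers specificity.
- *That a child with Day 0 severe AKI is RAI-positive by construction.* The scoring is in an additional file that is not shown. Overlap through creatinine is stated; its strength is not.
- *That Day 3 urine is used to predict Day 3 AKI.* The article describes collection over that period, partly for a repository. It does not say that Day 3 samples enter the models. The comparison with a Day 0 index suggests early samples, and an analysis plan that is not shown may name them.

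**Conclusion.** The point holds for the risk set. As written, persistent Day 0 stage 2–3 AKI is pooled with new AKI in the RAI and biomarker accuracy figures, and the article's own contrast between prediction and scoring existing injury cannot be tested from the pooled result. The expected direction is higher sensitivity and AUC, lower specificity where Day 0 AKI resolves, and little or no change in NPV.

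The size is unknown. The illustration gives a rise of 0.035 to 0.175 in sensitivity and 0.025 to 0.125 in AUC (before allowing for resolvers) for *f* of 10% to 50%. These figures rest on assumed rates and are not estimates for this study. The omission of a named urine sample is a matter for clarification, not an error. Overall this is an inexpensive improvement to a secondary aim and does not undermine the primary epidemiological objective.

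**What to change.** 1. Keep the all-comer analysis and label its outcome as new plus persistent AKI.
2. Pre-specify the same RAI and RAI-plus-biomarker measures in children without KDIGO stage 2–3 AKI on Day 0, and report the Day 0 AKI stratum separately. State whether Day 0 staging uses creatinine alone or also urine output.
3. Rest any claim to predict new AKI on the at-risk estimate.
4. As a secondary clarification, state that biomarkers compared with the Day 0 RAI come from an early index sample taken before the outcome day.

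**Cost.** This is a wording change. Day 0 AKI is already to be calculated, although Trial status shows recruitment still active at most centres. The price is precision. Under the assumed 12% rate and at-risk sensitivity of 0.60, the 95% half-width for sensitivity is 1.96 × √(0.24/567) = 0.040 at *f* = 10% and 1.96 × √(0.24/315) = 0.054 at *f* = 50%, against 1.96 × √(0.24/630) = 0.038 with all 630 events at the same sensitivity. In the urine subset (0.12 × 1,750 = 210 cases, of which 189 or 105 are new), the half-widths are 0.070 and 0.094. Some children may also lack an early sample, because urine is taken only in two daily time windows and only from children who are already catheterised.
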